### Study population, sample size, and power analysis

2.3

The data provided by the three health insurers Sanitas, CSS, and Helsana, comprise information on a total of 8422 primary care physicians in Switzerland. These primary care physicians treated at least one patient covered by one of the three health insurances. Due to the usual administrative processing delay of claims data of 6 months by health insurers, the definitive sample size calculation had to be based on claims data from January to December 2016. In this pre-randomization claims data set, we identified 3646 eligible GPs corresponding to the inclusion criteria, as mentioned above. A random sample of 220 physicians from the Basel area was left aside for a different interventional trial. The remaining study population of 3426 physicians were randomized to the intervention or control groups, with 1713 physicians in each arm.

We conducted a power analysis that was based on a trial simulation from 50 bootstrap samples. These bootstrap samples were extracted from the pool of physicians from the database of the year 2016, which was used to select and randomize GPs. The clinically relevant effect that the study aims to detect is, on average 5% expected reduction in prescription rates. Therefore, we simulated a trial for each bootstrap sample and we applied the effect which we expected to observe in the treatment arm. To also account for any variability, we simulated effects from distribution of potential effects, which were "centered" around 5%, for every physician. The standard deviation of the prescription rate in the target population was evaluated based on the data from the year 2016, which was 0.059 on the raw scale and 0.438 on the log scale. Also, we scaled the distribution to account for the expected proportion of non-responders of 15%. For each sample, we then tested the difference using a Mann Whitney *U* test (Wilcoxon rank-sum). Hence, we evaluated the power for each bootstrap sample, and derived medians and confidence intervals from the empirical distribution, which gave an estimated median power of 0.93 (95% CI: 0.90 to 0.96).

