### Randomization, treatment allocation, and blinding

2.4

All 3426 GPs were randomly allocated by a 1:1 ratio to the intervention and control group using R (R Core Team 2017 [20]). GPs in the intervention groups were formally blinded concerning the trial design, and GPs in the control group were fully blinded.

As all RCT relevant data are routinely collected by the automated procession of claims data of health insurances, the outcome assessment may also be considered as formally blinded.

Data analysis will be conducted by a statistician blinded for group assignment of physicians in the trial.

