### Outcomes

2.8

The primary outcome is the overall antibiotic use, defined as prescribed antibiotics per 100 patient consultations in the second year of intervention lasting from month 13 to month 24 (long-term intervention effect).

The secondary outcomes are (1) overall antibiotic use defined as prescribed antibiotics per 100 patient consultations from month 1–12 (first year of intervention, shorter-term intervention effect); (2) overall antibiotic use defined as prescribed antibiotics per 100 patient consultations over the entire intervention period from month 1 to month 24, with two repeated measurements, over the first and the second 12 month period of intervention; (3) use of broad-spectrum antibiotics (quinolones and oral cephalosporines) per 100 patient consultations; (4) hospitalizations rates (all-cause and related to infections based on Diagnosis Related Groups (DRG) definition); (5) Antibiotic use (prescribed antibiotics per 100 patient consultations) in five specific age groups, in patients 0–14 years, 15–24 years, 25–54 years, 55–64 years, and ≥65 years; and (6) secondary outcomes (3) to (5) will be evaluated separately over the second and first 12 months (from month 13 to month 24 and 1–12 months).

All cause hospitalization will be defined as any hospitalization (DRG-based) within 30 days after a preceeding GP consulation. Infection-related hospitalization will be defined as any hospitalization within 30 days after a preceeding GP consulation with DRG-codes for community acquired pneumonia, urinary sepsis, or sepsis. Reconsultation will be defined as any consultation within 30 days after a first GP consultation or any emergency consultation in a hospital.

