### Data analysis

2.11

Statistical analysis will be performed by the trial statistician using R (R Core Team 2017 [20]). All analyses will be conducted using the final dataset, which will be available in September 2020 (see also timeline in Fig. 1C) and will follow CONSORT guidelines and intention-to-treat principles [[22], [23], [24]]. A flowchart will describe the inclusion and follow-up of GPs by study arm. Baseline characteristics will be described by study arm with summary statistics such as median and interquartile range or number and percentage; no formal testing between arms will be performed [25]. Outcomes will be described by arm using summary statistics.

The primary outcome, the proportion of individuals with an antibiotic prescription in the second year of the intervention, will be assessed by ANCOVA modeling, with the outcome as a response, intervention (yes/no) as a factor of interest, and baseline year antibiotic prescription rate as a covariate (the baseline year is January–December 2017). Other baseline covariates of interest include comorbidities (based on pharmacy cost groups) patients' age, annual patient volume (total number of consultations per GP), and seasonality. For the primary outcome analysis, the coefficient estimates and their 95% CI will be reported. Secondary outcomes will be evaluated in the same way.

Effects for the period month 1 to month 24 will be modeled using a linear mixed model including the intervention (yes/no), time (baseline, first year, second year), an interaction term for the intervention with time, and by treating physician as random effects. Mean percentage changes from baseline will be derived for the intervention and control groups. Other baseline covariates of interest will be included as for the primary analysis.

The rates of hospitalizations and reconsultations will be modeled using logistic regressions including the intervention as a factor of interest and other relevant covariates. Hospitalization rates in the intervention and control group, with exact 95% CIs will be reported, and odds ratios for the intervention arm vs. control will be derived from the coefficients estimated for the logistic regression model.

The analysis in specific age groups will be similar to the primary analysis over the respective periods and stratified by age groups i) 0–14 years, ii) 15–24 years, iii) 25–54 years, iv) 55–64 years, and v) 65 years and over.

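### Hospitalization and reconsultation are analysed without accounting for the GP as the randomised unit, so their confidence intervals, as written, would be too narrow under any positive within-GP correlation

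*Protocol article*

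**What the plan says.** Section 2.4 of the protocol article makes the GP the unit of randomisation: "All 3426 GPs were randomly allocated by a 1:1 ratio to the intervention and control group". Section 2.3 gives the split, "with 1713 physicians in each arm".

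Section 2.8 defines the harm outcomes through what happens to a patient after a consultation. For admissions: "All cause hospitalization will be defined as any hospitalization (DRG-based) within 30 days after a preceeding GP consulation". Infection-related admissions use the same 30-day window. Reconsultation is tied to a first GP consultation or to a hospital emergency consultation.

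Section 2.11 then sets the analysis: "The rates of hospitalizations and reconsultations will be modeled using logistic regressions including the intervention as a factor of interest and other relevant covariates". Odds ratios for intervention against control come from the coefficients of that model. For admissions it adds: "Hospitalization rates in the intervention and control group, with exact 95% CIs will be reported". No random effect, generalised estimating equation (GEE), robust variance or overdispersion term is named for these outcomes. The preceding paragraph, on the month 1 to 24 linear mixed model, does name a physician term: "by treating physician as random effects".

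**The concern.** Patients of one GP share that GP's referral and recall habits, local hospital supply and case mix, so their outcomes tend to be correlated. When whole GPs are allocated to an arm, the precision of the comparison depends on variation between GPs as well as on the number of patients or consultations. A logistic model with no GP term, and an exact interval in its usual binomial form, both leave the between-GP part out.

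The article's Background and section 2.1 present hospitalization and reconsultation as the way to detect unintended effects of lower prescribing, and section 3.1 says the intervention could be continued systemwide if it proves efficacious. Intervals that are too narrow can produce a false difference in harm in either direction, or suggest that harm has been excluded more firmly than the data allow.

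**Working it through.** **The plan's own design figure.** The only one is the power for the primary outcome, 0.93 (section 2.3). Using 1713 GPs per arm, log-scale SD 0.438, the full 5% reduction and an assumed two-sided alpha of 0.05:

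- SE = 0.438 × √(2/1713) = 0.01497
- effect = −ln(0.95) = 0.0513, and 0.0513/0.01497 = 3.43
- power = Φ(3.43 − 1.96) = 0.929, in agreement with the stated figure

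That calculation takes the GP as the unit of analysis. There is no corresponding figure for hospitalization or reconsultation.

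**Inputs for the harm outcomes.** The only anchor for observations per GP, m, is the eligibility minimum of 100 patient contacts per year (section 2.2). The values m = 500 and 1000, and the ICC range of 0.001 to 0.01, are assumptions.

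**Formulas.** Design effect DE = 1 + (m − 1) × ICC. A correct interval is wider by √DE. The actual type I error of a nominal 5% test is 2 × [1 − Φ(1.96/√DE)], and the coverage of a nominal 95% interval is one minus that. For example, m = 100 with ICC 0.01 gives DE = 1 + 99 × 0.01 = 1.99, √DE = 1.41, 1.96/1.41 = 1.39, and a type I error of 16.5%.

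| m | ICC | DE | Width factor | Type I error | Coverage |
|---|---|---|---|---|---|
| 100 | 0.001 | 1.10 | 1.05 | 6.2% | 93.8% |
| 100 | 0.01 | 1.99 | 1.41 | 16.5% | 83.5% |
| 500 | 0.001 | 1.50 | 1.22 | 10.9% | 89.1% |
| 500 | 0.01 | 5.99 | 2.45 | 42.3% | 57.7% |
| 1000 | 0.001 | 2.00 | 1.41 | 16.6% | 83.4% |

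**Check by simulation.** There were 2000 null trials of 3426 GPs with beta-binomial events and equal m. Event rates and the between-GP coefficient of variation (CV) were assumed. The comparison columns are the odds-ratio test without a GP term, the exact interval for one arm's rate, and a comparison of GP-level rates.

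| m | Event rate | CV | Type I error, no GP term | Coverage, exact interval | Type I error, GP-level |
|---|---|---|---|---|---|
| 100 | 1% | 0.2 | 6.1% | 93.7% | 5.4% |
| 500 | 1% | 0.2 | 7.3% | 92.1% | 5.2% |
| 500 | 2% | 0.438 | 24.9% | 76.5% | 3.8% |
| 500 | 20% | 0.2 | 40.7% | 56.9% | 4.4% |

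The second row has an implied ICC of 0.0004, below the range in the first table, which is why its error is under 11%. The 20% rate stands for a common outcome such as reconsultation might be.

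**Does modelling rates per GP avoid the problem?** No. A grouped binomial logistic model on each GP's counts, with no overdispersion term, gives the same standard errors as the individual records with the same covariates.

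**Counting unit.** Section 2.8 links an admission to a consultation "within 30 days after a preceeding GP consulation". It does not say whether the record is the admission, the patient or the consultation. If every consultation were a record, one admission could be counted more than once, which would add within-patient correlation.

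**The case against.** The strongest reply is that this is a condensed article. The words ordinary and binomial do not appear in it, the covariates and the variance estimator are not listed, and a full protocol or analysis plan that is not shown could add a cluster term. This limits the claim to what the text would give as written. It does not remove the point, because exact intervals are positively specified for the hospitalization rates, and an analysis plan that handled clustering would have to depart from them. The general statement in section 2.11 that secondary outcomes are evaluated like the primary does not help either, since the specific logistic paragraph displaces it.

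A reader might take the physician random effect in the neighbouring model as evidence that clustering was deliberately left out here. The documents do not support that: the mixed model has three time points per GP and needs the term for repeated measures.

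A reader might also infer that admissions will be counted several times. Section 2.8 can equally be read as counting each admission once, and for reconsultation it refers to a first consultation. Only the lack of a stated unit can be held against the text. Likewise, exact intervals are stated for hospitalization and not for reconsultation.

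The objection to size also stands in part. For rare events at about 100 contacts per GP, the simulated error is near 6%. Covariates that explain differences between GPs would lower the residual correlation further.

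**Conclusion.** The point holds for the methods as stated. With GPs randomised and no GP-level term, the odds-ratio intervals for hospitalization and reconsultation, and the exact intervals for hospitalization rates, are too narrow under any positive within-GP correlation.

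The direction is firm; the size cannot be fixed from the document. For assumed ICCs of 0.001 to 0.01, type I error is about 6% to 17% at 100 observations per GP and about 11% or more at 500 or more. A statement that false signals would occur well above 5% of the time in every case is not supported: the lower end is close to nominal, and ICCs below the assumed range are possible for rare admissions.

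These are secondary outcomes, with no margin or power claim attached to them in the article. The primary analysis and its power calculation are not affected.

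**What to change.** In section 2.11:

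- Fit the logistic models for both outcomes with a GP random intercept, or with GEE or sandwich variance clustered on GP. State which, since the first gives a GP-conditional odds ratio and the others a population-averaged one.
- Replace the exact intervals for the arm-level hospitalization rates with GP-cluster-adjusted ones, by sandwich variance or by a bootstrap that resamples GPs.
- State the counting unit and count each admission once, for example with one record per patient and period and a rule attributing it to a GP. This matters most with a random intercept, which does not by itself absorb repeated records of one patient.

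The pseudonymised physician and patient identifiers are already in the dataset (Table 1 in section 2.10), so no new data are needed. The cost is a change of wording, a little more analysis work and wider reported intervals.

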### Ethics and dissemination

2.12

The study trial protocol was approved by the lead ethics committee Ethikkommission Nordwest-und Zentralschweiz (EKNZ Project-ID 2017-00888) according to the simplified approval procedure based on Art. 34 "Absence of informed consent" of the Human Research Act (HRA) and based on Art. 37–40 "Use of Biological Material and Health-Related Personal Data for Research in the Absence of Informed Consent" of the Human Research Ordinance (HRO). Without further requests by the lead ethics committee, the approval of the lead ethics committee is valid for all remaining cantons of Switzerland.

## Discussion

3

To our knowledge, this is the first pragmatic RCT using routinely collected patient level claims data to assess the effects of quarterly personalized prescription feedback on antibiotic prescribing in primary care on the national health system level. In our pilot RCT [12,21], feedbacks and final analyses were based on monthly aggregated claims data, and not on patient-level data. As a consequence, the analyses, including subgroups, were limited because of the aggregated nature of the data. Built on the experience of the pilot RCT, we planned the present trial protocol using patient-level data from routinely collected claims data. For instance, a more comprehensive quarterly feedback to GPs (prescribing rates instead of defined daily doses) and the patient-level data will allow for more detailed analyses of antibiotic prescribing patterns and to correlate them for example with test ordering like CRP, pharyngeal swabs or urine cultures.

Moreover, patient-level data allows for investigating multiple antibiotic prescribing in the same patient and the analysis of potentially unintended consequences of the intervention like hospitalization, emergency ward consultations, and reconsultations due to untreated bacterial infections. We will also receive detailed data on ordering of diagnostic laboratory tests, X-rays and referals to specialists that are relevant for the management of respiratory and urinary tract infections. This will allow for secondary analysis of physician practice patterns and antibiotic prescribing and provide useful data for the planned health economic analyses.

## Strengths and limitations

3.1

Our pragmatic trial design will allow to generate evidence of high internal and external validity on the effectiveness of antibiotic prescribing feedback in primary care, due to the randomized trial design and blinding for the nature of the intervention, and the use of routinely collected claims data, which assures continuous and complete follow-up data with no interference with daily routine for data collection. Full blinding of the control group by use of Zelen's design [26] allows for a comparator that reflects the actual practice of antibiotic prescribing in primary care in Switzerland at large. If our feedback intervention proves to be efficacious, the intervention could be continued systemwide as the infrastructure has been established for the purpose of this trial. This would allow continuous monitoring of antibiotic prescribing at low costs and to intervene if peer-based prescribing benchmarks are constantly overrun by some GPs.

## Declarations

Ethics approval and consent to participate.

The study trial protocol was approved by the lead ethics committee Ethikkommission Nordwest-und Zentralschweiz (EKNZ Project-ID 2017-00888) according to the simplified approval procedure based on Art. 34 "Absence of informed consent" of the Human Research Act (HRA) and based on Art. 37–40 "Use of Biological Material and Health-Related Personal Data for Research in the Absence of Informed Consent" of the Human Research Ordinance (HRO). Without further requests by the lead ethics committee, the approval of the lead ethics committee is valid for all remaining cantons of Switzerland.

## Patient and public involvement

It was not appropriate or possible to involve patients or the public in the design, or conduct, or reporting, or dissemination plans of our research.

## Consent for publication

Not applicable.

## Availability of data and materials

No additional data to be shared.

